## Abstract

**Background:**

Older inpatients are at risk of hospital-associated geriatric syndromes including delirium, functional decline, incontinence, falls and pressure injuries. These contribute to longer hospital stays, loss of independence, and death. Effective interventions to reduce geriatric syndromes remain poorly implemented due to their complexity, and require an organised approach to change care practices and systems. Eat Walk Engage is a complex multi-component intervention with structured implementation, which has shown reduced geriatric syndromes and length of stay in pilot studies at one hospital. This study will test effectiveness of implementing Eat Walk Engage using a multi-site cluster randomised trial to inform transferability of this intervention.

**Methods:**

A hybrid study design will evaluate the effectiveness and implementation strategy of Eat Walk Engage in a real-world setting. A multisite cluster randomised study will be conducted in 8 medical and surgical wards in 4 hospitals, with one ward in each site randomised to implement Eat Walk Engage (intervention) and one to continue usual care (control). Intervention wards will be supported to develop and implement locally tailored strategies to enhance early mobility, nutrition, and meaningful activities. Resources will include a trained, mentored facilitator, audit support, a trained healthcare assistant, and support by an expert facilitator team using the i-PARIHS implementation framework. Patient outcomes and process measures before and after intervention will be compared between intervention and control wards. Primary outcomes are any hospital-associated geriatric syndrome (delirium, functional decline, falls, pressure injuries, new incontinence) and length of stay. Secondary outcomes include discharge destination; 30-day mortality, function and quality of life; 6 month readmissions; and cost-effectiveness. Process measures including patient interviews, activity mapping and mealtime audits will inform interventions in each site and measure improvement progress. Factors influencing the trajectory of implementation success will be monitored on implementation wards.

**Discussion:**

Using a hybrid design and guided by an explicit implementation framework, the CHERISH study will establish the effectiveness, cost-effectiveness and transferability of a successful pilot program for improving care of older inpatients, and identify features that support successful implementation.

**Trial registration:**

ACTRN12615000879561 registered prospectively 21/8/2015.

## Background

People aged 65 and over account for more than half of hospital bed days [1], and their stay is commonly complicated by non-disease specific complications known as geriatric syndromes [2–5]. Delirium, functional decline, falls, incontinence and pressure injuries occur frequently in older inpatients, and represent the interaction between baseline vulnerability (conceptualised as frailty), acute illness or surgery and the hospital care environment [6–8]. Hospital-associated geriatric syndromes share risk factors including functional impairment, mobility impairment, cognitive impairment and malnutrition. They frequently co-exist, and are associated with longer hospitalisations, increased dependency and greater risk of institutional care and death [2, 3, 5, 8–10].

Integrated, multi-component interventions which address the common shared risk factors can significantly reduce the risk of geriatric syndromes and may reduce hospital length of stay [8, 11–13]. Components include “basic” strategies such as encouraging early mobilisation and functional independence, supporting nutrition and hydration, and providing reorientation and meaningful personal engagement. However, these strategies are not consistently applied within the complex acute care system [6, 14, 15]*,* with recognition of a large number of barriers at the level of the patient (e.g. symptoms, motivation), staff (e.g. knowledge, attitudes, time, skills, responsibility, leadership) and system (e.g. culture, resources, competing priorities) [16–23].

Eat Walk Engage [24] is a complex multi-component intervention designed to identify and address these barriers on non-geriatric wards. A complex intervention is one with multiple components, behaviours, groups, and/or outcomes impacted [25]. Eat Walk Engage aims to improve early mobility and functional independence, enhance oral nutritional intake, and improve opportunities for interactions and meaningful cognitive activities. The program uses the integrated Promoting Action on Research Implementation in Health Services (i-PARIHS) framework designed to support implementation of complex interventions [26]. A skilled facilitator assists the local multidisciplinary team (MDT) to prioritise areas for improvement, identify barriers and enablers, develop solutions tailored to the local context, and evaluate using iterative cycles of change and measurement [26]. In pilot studies, Eat Walk Engage decreased hospital-acquired geriatric syndromes and decreased length of stay [24, 27].

The Collaborative for Hospitalised Elders: Reducing the Impact of Stays in Hospital (CHERISH) study will be a hybrid evaluation of Eat Walk Engage, using outcome and process evaluation to study both intervention effectiveness, and the change processes involved in implementation [28]. The aim of the outcome evaluation is to evaluate the effectiveness and cost-effectiveness of the Eat Walk Engage program for inpatients aged 65 years and older receiving care on medical and surgical wards. The resources, interventions, goals and hypothesised outcomes of the program are outlined in Table 1. The main CHERISH study hypotheses are that, compared to control wards, wards implementing Eat Walk Engage will demonstrate:Reduction in hospital-related geriatric syndromes (delirium, functional decline, falls, pressure injuries and new incontinence)Reduction in length of stay under the treating teamReduction in institutional care (rehabilitation or other subacute care, hospital transfers, or new residential aged care placement).

**Table 1 Tab1:** Eat Walk Engage program resources, intervention components, program goals, outcomes and evaluation methods. FTE full time equivalent. MDT existing multidisciplinary team

RESOURCES	INTERVENTION COMPONENTS	PROGRAM GOALS	OUTCOMES
Trained Eat Walk Engage facilitator (0.4 FTE per ward) Expert facilitation team Trained Eat Walk Engage assistant (0.5 FTE per ward)	Under guidance of the facilitator: • MDT develops shared understanding and improvement goals • MDT identifies local barriers and enablers for nutrition, mobility and cognitive engagement • MDT clarifies roles and opportunities for delegation to assistant • MDT initiates small cycle improvements with re-evaluation	Higher proportion of older patients achieve: • Early and adequate nutrition • Early mobility and independence • Meaningful activities and participation	Geriatric syndromes Length of stay Institutional discharge Health care costs
Program staff costs Training materials and time	i-PARIHS mapping Baseline interviews, audits MDT meeting minutes Facilitator journals Facilitator interviews MDT service patterns	Patient interviews Activity mapping Mealtime audits	Geriatric syndromes Length of stay Discharge destination 30 day health status Hospital readmissions

A cost-effectiveness evaluation will determine whether improvements in health benefits measured in quality adjusted life years are justified against the additional costs of implementing the program. The process evaluation will help to understand how and where the program worked, by testing the effect on care processes and outcomes (Table 1) and by exploring how key contextual features of different sites contributed to implementation success or failure.

## Methods

### Setting

The study will be conducted in four hospitals, including two metropolitan teaching hospitals and two large regional hospitals, in two Hospital and Health Services (HHS) serving populations in South-East Queensland, Australia. During study planning, senior clinical and administrative leaders from these hospitals committed resources to participate in this partnership project, and have assisted the study team to identify two medical or surgical wards in each hospital admitting at least 50% of admitted patients aged over 65, which are suitable for participation in the study. The 8 selected wards are three general medical wards, two specialty medicine wards, one orthopaedic ward and two general surgical wards.

### Study design

We will use a cluster randomised control design, randomising one ward within each hospital (cluster) to implement the Eat Walk Engage program (intervention) and the other to continue usual care (control). Allocation will be undertaken by the off-site study statistician based on computer-generated random numbers using R [29].

Data will be collected on all 8 wards before and after an intervention period, with additional process data collected during implementation on intervention wards (Fig. 1). Outcome evaluation will compare measures in pre-intervention and post-intervention samples on the intervention wards, compared to measures in samples from the same time on control wards. This study design allows measurement of changes in processes and outcomes following intervention (to understand mechanisms of any observed outcome improvement) while controlling for systematic changes at hospital level which may affect the outcomes of interest. Patient-level data collection is planned for October 2015-March 2016 (pre-intervention) and October 2016-March 2017 (post-intervention).

The site facilitator will identify and prepare members of the ward-based multidisciplinary team (MDT, including senior nursing staff, physiotherapist, occupational therapist, dietitian, social worker, speech pathologist, assistant staff, medical staff and others). They will engage MDT members as local champions and informal leaders, both informally and through monthly team meetings. The facilitator will obtain patient feedback through structured interviews and will use a suite of process measures described below to assess current performance. These data will be fed back to the MDT to help them reach consensus on priorities for improvement and to identify potential barriers, enablers and solutions. Solutions might include individual or team actions, or changes to systems or resources. For example, if the baseline data suggests gaps in achieving early mobility, barriers identified by patients and staff might include inadequate pain control, inadequate encouragement, poor team communication of mobility goals, insufficient walking aids, and no walking destination. Solutions in that setting will require consideration of patient assessment, patient and team communication, and ward equipment and design, but may also require support by education and leadership, and multiple interacting strategies may be required to produce measureable improvements. The facilitator will support MDT members using strategies such as marketing, team building, role clarification, audit and feedback, reminders and education. The facilitators will also be encouraged to develop networks, leadership support and monitoring mechanisms at each site, important for sustaining changes [30, 31]. A senior physician designated as the site investigator will support the facilitator and MDT.

Previous successful programs have described an assistant workforce to help ward staff ensure consistent provision of basic care interventions, although the type of assistant varies between models (e.g. trained volunteers [32], nursing assistants [33] or healthcare students [34]). Intervention wards will be provided with a half-time trained multi-professional healthcare assistant, who will undertake self-directed tasks (e.g. providing reading materials, mealtime set-up, reorientation), as well as specific individual or group interventions delegated by health professionals (e.g. assisted mobilisation, exercise programs, encouraging supplement consumption, reminiscence strategies) to support the MDT strategies. The assistant will be recruited locally and undertake training and competency assessment at a central site, with mentoring by the facilitator and MDT, and peer support by monthly teleconference.

### Outcome evaluation

#### Participants and measures

Patients will be eligible to participate if they are aged 65 years or older, and admitted to any study ward during the study period, with an anticipated length of stay of three days or more. Exclusions are patients receiving end of life care, outliers from other teams, patients transferred or discharged from the ward within three days, and those with critical illness or severe cognitive impairment who cannot consent to participate and lack a surrogate able to consent on their behalf. Participants can only be enrolled once in the same study period, but the same participants could potentially be enrolled in both the pre-intervention and post-intervention samples during different hospital admissions.

Data will be collected by trained research assistants from patient (or surrogate) interview at four time points: admission (including assessment of health status prior to admission), day 5 of hospitalisation, discharge and 30 days after discharge from the treating team (the 30-day interview is by telephone). Data items for each interview are shown in Table 2. Additional data from structured review of the medical record will include demographics, diagnosis assigned by the treating team, co-morbidities, number of prescribed medications, previous hospitalisations, admission nursing assessments of common risk factors (vision, hearing, falls, pressure injuries, functional status, cognitive status, continence status), and consultations from allied health professional and other specialties. Baseline data from interview and medical record will be used to construct a frailty index based on the deficit accumulation model [35].

**Table 2 Tab2:** Interview data collection items and timing. Descriptions and references are included in main text

	Pre-admission	Admission (within72 h)	Day 5	Discharge (within 24 h)	Day 30
ADL	X	X	X	X	X
IADL	X				X
Malnutrition Screening Tool		X			
Depression (PHQ-2)	X				
Self-rated health	X				
Falls	X		X	X	X
Pressure injury		X	X	X	X
Bladder incontinence	X	X	X	X	X
Bowel incontinence	X	X	X	X	X
SPMSQ		X	X	X	X
3D-CAM		X	X	X	
EQ-5D				X	X

ADL activities of daily living: count of basic ADL (bathing, dressing, toileting, transferring, walking across and room, and feeding) requiring human assistance

IADL instrumental activities of daily living: count of instrumental activities (shopping, cooking, housework, transport, using the telephone, managing medications, managing finances) requiring assistance

*PHQ-2* Patient Health Questionnaire-2, *SPMSQ* Short Portable Mental Status Questionnaire, *3D-CAM* 3 min diagnostic assessment for CAM-defined delirium, *EQ 5D* EuroQol health questionnaire

#### Outcomes

The two primary outcomes are any hospital-associated geriatric syndrome and length of hospital stay. Any hospital-associated geriatric syndrome is a composite measure including one or more of delirium, functional decline, falls, pressure injury or new incontinence occurring during the stay under the treating team. These are common, potentially preventable, and associated with poor outcomes [2]. Functional decline is defined as any increase in the number of basic activities of daily living between baseline 2 weeks prior to admission and discharge from the treating team [36]. Delirium is defined by positive 3-min Confusion Assessment Method (3D-CAM) [37] at admission, day 5 or discharge assessment, and/or evidence of delirium in structured medical record screening, as this provides the most sensitive ascertainment of delirium [38]. Falls and pressure injuries are defined as an event reported by the patient at admission, day 5 or discharge assessment, and/or documented evidence in the medical record. New urinary or faecal incontinence is defined as patient-reported incontinence at admission, day 5 or discharge, and/or documented evidence in the medical record, in those participants who reported being continent prior to admission.

Secondary outcomes will include each of the individual geriatric syndromes defined above; discharge destination (home or institutional care); 30-day health status including mortality, readmission, functional status and quality of life; and 6-month readmission and hospital utilisation. Hospital utilisation and readmissions will be obtained from a state-wide database of all public hospital admissions. Quality of life will be assessed using a preference-based utility score (EQ5D) [39] administered at discharge (face-to-face) and 30 days after discharge (telephone) in consenting participants in both groups, enabling estimation of quality adjusted life years gained. Costs to the healthcare system will include implementation costs (project, clinical and management staff time, consumables and overheads) and health services utilisation costs based on length of stay (initial, continuing and readmissions) and costs incurred from adverse events.

Research assistants for each site will be health professionals who are not ward staff and not involved in study design or delivery of interventions. They will undertake a 2-day training course, with a detailed data collection manual of procedures, definitions, and frequently asked questions. They will be supported by site visits by the data manager, weekly teleconference, and telephone and email support throughout the data collection period. Specific training in 3D-CAM delirium assessment will be provided using scored video vignettes provided by the developers and practice scoring of 3 patients under supervision of the chief investigator. Reliability of chart data extraction will be checked by re-abstraction of 5 – 10 charts at each site by the chief investigator and project manager within the first few weeks of project commencement. Data will be entered directly into a secure web-based data collection and management system (RedCAP), with real time data monitoring by the data manager to optimise completeness and integrity of data.

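### The primary composite is limited to syndromes arising during the stay, but its rules for delirium, falls and pressure injury accept admission findings with no present-on-admission exclusion, and the falls rule contradicts Table 2

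*Protocol article*

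**What the plan says.** All references are to the protocol article.

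- **Scope (Outcomes).** The composite requires "one or more of delirium, functional decline, falls, pressure injury or new incontinence occurring during the stay under the treating team".
- **Delirium (Outcomes).** "Delirium is defined by positive 3-min Confusion Assessment Method (3D-CAM) [37] at admission, day 5 or discharge assessment", and/or evidence from structured screening of the medical record.
- **Falls and pressure injuries (Outcomes).** "Falls and pressure injuries are defined as an event reported by the patient at admission, day 5 or discharge assessment", and/or documentation in the medical record.
- **Incontinence (Outcomes).** Counted only "in those participants who reported being continent prior to admission".
- **Functional decline (Outcomes).** An increase in dependent basic activities "between baseline 2 weeks prior to admission and discharge from the treating team".
- **Table 2 (Participants and measures).** The admission assessment is made within 72 h. Falls are asked about for pre-admission, day 5, discharge and day 30, with no admission entry. Pressure injury and 3D-CAM are recorded at admission and have no pre-admission entry.
- **Analysis.** The comparison concerns participants developing a syndrome. Power is stated as 80% for a 30% reduction from a 40% baseline, with 250 participants per arm in each period.

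**The concern.** The scope sentence and the component rules give two different endpoints. Under the scope sentence, a patient who arrives delirious or with a pressure injury, and develops nothing further, is not a case. Under the component rules the same patient is a case, because a positive admission finding is sufficient. Two of the five components show how a prior-status condition can be written; the other three have none.

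For falls, the Outcomes text and Table 2 cannot both be followed. Either the admission clause has no interview item behind it, or the pre-admission item would have to supply it. One of the eight wards is orthopaedic (Setting), where a fall before admission is a plausible reason for being there.

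A ward program cannot prevent what was present before the patient arrived. Such cases add equally to both arms on average and pull the relative effect toward the null. If their share changed between periods by a different amount in the two arms, bias would be added to the loss of power. The individual syndromes are secondary outcomes under the same definitions, so they are affected too.

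**Working it through.** **1. Does each rule separate new from pre-existing cases?**

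| Component | Prior-status or onset condition in the rule | Item in Table 2 at admission / pre-admission |
|---|---|---|
| Delirium | none | yes / no |
| Falls | none | no / yes |
| Pressure injury | none | yes / no |
| Incontinence | continent before admission | yes / yes |
| Functional decline | change from 2 weeks before admission | yes / yes |

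The first three rules do not carry out the scope sentence.

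**2. Reproduce the plan's power.** Inputs from Analysis: p1 = 0.40; p2 = 0.40 × 0.70 = 0.28; n = 250 per arm. Two-sided alpha of 0.05 is assumed, in line with the 95% intervals.

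Power = Φ[(|p1 − p2| − 1.96·s0) / s1], where s0 = √(2·p̄(1 − p̄)/n), s1 = √((p1(1 − p1) + p2(1 − p2))/n) and p̄ = (p1 + p2)/2.

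With p̄ = 0.34, s0 = 0.0424 and s1 = 0.0420, (0.12 − 0.0830)/0.0420 = 0.88, so power is 81%. The stated 80% is reproduced as a simple comparison of 250 with 250, with no allowance for clustering or for the pre/post contrast. The same calculation is used below only to show the cost of the definition.

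**3. Dilution, on an assumed share.** Let a be the number of the 40 baseline points made up of patients who qualify only through a pre-existing finding. The documents do not give a; 5, 10 and 15 points are assumptions. With a true 30% reduction in the rest:

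- cases kept: p1 = 0.40 and p2 = 0.40 − 0.30 × (0.40 − a);
- cases not counted (patients stay in the denominator as event-free): p1 = 0.40 − a and p2 = 0.70 × (0.40 − a).

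| a | Kept: p1 v p2 | Observed reduction | Power, kept | Not counted: p1 v p2 | Power, not counted | Difference |
|---|---|---|---|---|---|---|
| 5 points | 40% v 29.5% | 26% | 69% | 35% v 24.5% | 73% | about 4 points |
| 10 points | 40% v 31.0% | 22.5% | 56% | 30% v 21.0% | 64% | about 8 points |
| 15 points | 40% v 32.5% | 19% | 41% | 25% v 17.5% | 54% | about 12 points |

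Not counting these cases restores the 30% relative reduction and gives more power than keeping them, despite the lower event rate. The cost of the definition is the last column. The drop from 81% is not the right measure, because most of it comes from the lower rate of preventable events and remains after the fix.

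**The case against.** The strongest reply is that the scope sentence already governs. On that reading the component sentences only say how events within the stay are ascertained, and the detailed data collection manual mentioned under Outcomes may hold the dating rules. This is a fair account of the likely intent. It does not settle the matter, because the component rules are written as definitions that a positive admission finding satisfies on its own.

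Other points that stand in whole or part:

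- **Admission is not arrival.** The assessment may take place up to 72 h into the stay, so some admission positives begin on the ward. A reader might infer that every admission finding predates the stay; the documents do not support that.
- **Falls.** A reader might infer that the fall leading to an orthopaedic admission is meant to count. Table 2 records earlier falls separately from those at day 5 and discharge, which points the other way. What is shown is a contradiction between text and table.
- **Sensitive ascertainment.** The protocol gives this as its reason for combining 3D-CAM with chart review. It bears on detection and does not address time of onset.
- **Admission nursing assessments.** Participants and measures lists these as risk-factor data. That they would feed the pressure-injury outcome is possible under the documentation clause, but is not stated.
- **Co-existing syndromes.** The Background says syndromes often occur together, so many patients with a pre-existing finding would be cases anyway. Only those with no other qualifying event dilute the effect.
- **Concurrent controls.** The comparison of pre/post change between arms removes stable differences in admission mix, and Analysis provides for checking changes in patient characteristics and adjusting. A reader might infer that the definition biases the result; that requires a shift in mix that differs between arms. Attenuation does not.
- **Remaining components.** Functional decline and incontinence can also include loss between the pre-admission baseline and ward arrival, so correcting three components does not give an endpoint made up only of ward-preventable events.

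**Conclusion.** The point holds as a conflict within the definition of a primary outcome. The scope is limited to the stay, while the rules for delirium, falls and pressure injury accept admission findings without a present-on-admission exclusion. The falls rule also disagrees with Table 2. Followed as written, the rules admit an unknown share of pre-existing cases and attenuate the effect.

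The direction is clear; the size cannot be derived from the documents. On assumed shares of 5, 10 and 15 of the 40 points, the observed reduction is 26%, 22.5% and 19% in place of 30%, and the definition costs about 4, 8 and 12 points of simple two-group power. The largest share is 37.5% of all cases (15/40) and should be read as an upper illustration. If the 40% and 30% planning figures came from data using the same definition, the stated power already absorbs the dilution. The documents do not show that the protocol intends to count earlier events, or that bias, as distinct from lost power, will occur.

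**What to change.** Amend the component definitions, for the composite and the individual syndromes, before outcome data are compared by arm:

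1. **Falls.** Count only the day 5 and discharge reports and chart entries dated within the stay under the treating team. This agrees with Table 2.
2. **Pressure injury.** Count only injuries not present at the admission assessment or in the admission nursing assessment.
3. **Delirium.** Exclude delirium with evidence of presence on arrival. For a positive admission 3D-CAM of unclear onset, state one rule in advance.
4. **Sensitivity analysis.** Repeat the primary comparison with the alternative, that is the current broad definition, and report present-on-admission cases by arm and period so that any shift in admission mix can be seen.

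The cost is mainly wording, since the admission 3D-CAM, the admission pressure-injury item, the admission nursing assessments and chart review are already planned. Chart abstraction must record event dates if it does not already. The downside is a lower event rate and the loss of some early ward-onset events, mostly delirium and pressure injury first seen within the 72 h window; the sensitivity analysis shows how much this matters.
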